### 2.2. Outcomes

#### 2.2.1. Primary Outcome

The primary objective of this study is to evaluate the feasibility of the intervention in the PCP setting. Using a qualitative approach, we will evaluate feasibility and acceptance as well as barriers and facilitators of the implementation. Routine care data will quantitatively inform about the number of patients with CHD potentially reached by the minimally invasive intervention. In addition, we will assess recruitment success and the rate of study completion.

#### 2.2.2. Secondary Outcomes

Changes in PCP behaviour, operationalised by primary care routine data in the practice management system related to MCD. This includes patient-level information on diagnoses, medication prescription, referral to specialists, and billing codes of diagnostic and therapeutic measures related to MCD.Influence of organisational characteristics on patient-level outcomes of the implemented intervention, operationalised by a daily workload statistic (i.e., the total number of patients treated per day per PCP) derived from routine data and a questionnaire assessing basic information regarding the participating PCPs, practice structures and treatment processes.Cumulative socio-economic return calculated by a formative socio-economic impact assessment (SEIA) for different implementation scenarios to support future implementations strategies.

### 2.3. Data Collection

Data in Part I of the study will be collected from individual narrative interviews using a semi-structured interview guide. Interviews will take place face-to-face or via videoconference and are scheduled for approximately 60 min. Previous studies indicate that data quality from video interviews is not of inferior quality compared to traditional, face-to-face interviews and that rapport is comparable [40,41]. Two researchers who are trained in semi-structured interviewing will conduct the interviews. Interviews will be recorded, transcribed verbatim by an external professional transcription service and anonymised. The semi-structured qualitative interview guide [42] includes three thematic blocks of approximately 20 min each: (1) experiences and requirements for identification and standardised care of patients with CHD and MCD, (2) presentation/discussion of the planned intervention and (3) barriers and facilitators of planned intervention and of the implementation in PCP offices. During the interviews, participants will be presented with drafts of the booklet and the QPS for patients.

For Part II, qualitative and quantitative data will be collected at different time points. A detailed description of the variables is provided in Table 1. Organisational characteristics will be collected via questionnaire at the beginning of the intervention period and entered into electronic case report forms. Anonymous routine care data as well as the daily workload statistics per PCP will be exported from practice management systems via a service provider. The data export will take place once per PCP office for each PCP separately at the end of the intervention phase and retroactively extract all relevant information from the preceding twelve months (six-month pre-intervention observation period and six-month intervention period). The day of the training course with the PCP marks the start of the six-month intervention phase. Qualitative interviews to evaluate the intervention will be conducted in line with the procedure of Part I described above. A schematic depiction of the study flow and data collection is provided in Figure 2.

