### 2.5. Data Analysis

Data analysis will be based on a combination of quantitative and qualitative analysis methods. The transcripts of the interviews in Parts I and II will be entered into MAXQDA software (VERBI GmbH, Berlin, Germany) and analysed following Miles and Huberman [42]. The software program MAXQDA will be used for the qualitative data analysis and supports the systematic evaluation and interpretation of the transcript. Qualitative content analysis will be chosen to explore the unique perspectives of the participants and to systematically extract the content to a descriptive level. To provide validity of data interpretation, transcripts will be independently coded by two researchers. A coding framework will be developed that combines deductive and inductive approaches. The deductive approach will draw on extant concepts for implementation of patient-centred care [43] as well as the Consolidated Framework for Implementation Research [44].

Descriptive and explorative methods will be used to analyse the quantitative routine data. To investigate the influence of the intervention on PCP behaviour, we will conduct repeated measures analyses to compare the frequency of diagnostic and therapeutic actions, referrals and medication prescription before and after the training course. In this context, the influence of organisational characteristics as well as the intervention adherence, as reported in the interviews, will be taken into consideration. In addition, we will record and analyse reasons for dropout or non-adherence to the study procedures. Data from PCP offices will be included in the analysis if a minimum of 80% (≥20 weeks) of the intervention phase has been completed before dropout. To reduce the risk of dropout, regular check-ins with the PCP offices will be carried out via e-mail or phone.

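### One export at the close of the intervention phase leaves little or no time for late entries after training; if recording is delayed, the exploratory before-after comparison leans against the intervention (minor)

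*Protocol article*

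**What the plan says.** Section 2.3 (Data Collection) fixes the timing: one export per PCP office, made for each PCP on its own, is to run "at the end of the intervention phase and retroactively extract all relevant information from the preceding twelve months". The look-back covers "the preceding twelve months (six-month pre-intervention observation period and six-month intervention period", and the boundary between the windows is set by T0: "The day of the training course with the PCP marks the start of the six-month intervention phase". The data are "exported from practice management systems via a service provider". No second export and no waiting period is mentioned.

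Section 2.2.2 defines change in PCP behaviour through recorded diagnoses, prescriptions, referrals and "billing codes of diagnostic and therapeutic measures related to MCD". Section 2.5 will "compare the frequency of diagnostic and therapeutic actions, referrals and medication prescription before and after the training course", using descriptive and exploratory methods.

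Against incomplete routine data, section 2.5 names three measures: limiting the export to items that practices record reliably, filters that tolerate misspellings, and plausibility checks for technical faults in the export.

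**The concern.** The outcome is a count of entries in the practice's own system, and the two windows being compared differ in age when that system is read. A pre-training action has at least six months to be documented before the export. An action in the last weeks after training may have only days. Any lag between acting and recording therefore removes entries almost entirely from the post-training side.

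None of the three measures in section 2.5 would catch this. Choosing reliably recorded items concerns whether something is recorded, not when. The spelling filters and the technical checks would both pass a file in which some entries have not yet been made.

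The study has no control group, so there is no parallel series exported on the same day in which the same shortfall would show. The Discussion expects the results to guide a later RCT, so an understated change in PCP behaviour could carry over into its planning.

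**Working it through.** **The plan's own figure.** Section 2.1.2 assumes 900 patients per PCP per quarter and 10% with CHD: 900 × 0.10 = 90. Times 10 offices this is 900 per quarter, and times 2 quarters it is 1800 cases per window. The figure reproduces. These are CHD patients counted by quarter, not MCD-related entries.

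**Age of records at export.** If the export falls at month 6 after T0, pre-training records are 6 to 12 months old and post-training records 0 to 6 months old. The wording leaves little room for a later date. If the export ran 4 weeks later and reached back twelve months from that day, it would lose the first 4 pre-training weeks and add 4 weeks after the window, and the twelve months would no longer be the two study windows.

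**Size under assumed delays.** The article gives no delay, so these inputs are assumptions. Entries arise evenly over 26 weeks per window. A share s is entered late, with an exponential delay of mean m weeks, and the export runs g weeks after the window closes. For a window whose records are a to b weeks old at export,

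missing share = s × m × (e^(−a/m) − e^(−b/m)) / (b − a),

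with (a, b) = (g, 26 + g) after training and (26 + g, 52 + g) before. With no true change, the observed after/before ratio is (1 − missing after) / (1 − missing before).

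Example with s = 0.3, m = 4, g = 0:
- After: 1.2 × (1 − e^(−6.5)) / 26 = 0.0461.
- Before: 1.2 × (e^(−6.5) − e^(−13)) / 26 = 0.00007.
- Ratio: 0.9539 / 0.99993 = 0.954.

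| Late share, mean delay | Missing after (g = 0) | Missing before (g = 0) | Ratio, g = 0 | Ratio, g = 4 | Ratio, g = 13 | True +10% seen as (g = 0) |
|---|---|---|---|---|---|---|
| none | 0 | 0 | 1.000 | 1.000 | 1.000 | +10.0% |
| 10%, 2 weeks | 0.77% | 0.000% | 0.992 | 0.999 | 1.000 | +9.2% |
| 10%, 4 weeks | 1.54% | 0.002% | 0.985 | 0.994 | 0.999 | +8.3% |
| 30%, 4 weeks | 4.61% | 0.007% | 0.954 | 0.983 | 0.998 | +4.9% |
| 30%, 8 weeks | 8.87% | 0.344% | 0.914 | 0.948 | 0.983 | +0.6% |
| all, 4 weeks | 15.36% | 0.023% | 0.847 | 0.944 | 0.994 | −6.9% |

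The last column is 1.10 × ratio − 1. Reversing a true 10% rise takes a ratio below 1/1.10 = 0.909, a shortfall of more than 9.1%. None of the four partial-delay rows reaches that.

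**Dropping final weeks instead.** With 30% late by a mean of 4 weeks and the last 4 weeks dropped from each window, the post-training records kept are 4 to 26 weeks old. The missing share is 1.2 × (e^(−1) − e^(−6.5)) / 22 = 0.020, against 0.046 for the full window.

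**The case against.** Five points can be made for the plan.

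- The text says the export is at the end of the phase, not on its last day. Figure 2, which shows the collection time points, is not reproduced in the text reviewed, and the full protocol may state a lag. This stands in part: no day is fixed. But equating the preceding twelve months with the two windows leaves little room for a run-out.
- Nothing in the article says that practices enter or correct records late, by how much, or for which items. This stands fully. With prompt entry there is no effect whatever the export date, and delays may differ between prescriptions, referrals, diagnoses and billing codes.
- The choice of reliably recorded items is a real measure against incomplete data. It is, but it does not address lateness.
- The comparison is secondary and exploratory in a ten-office feasibility pilot, and the Limitations section already concedes that the lack of a control group restricts inference on effect. This stands and governs the severity.
- A sensitivity analysis is commonly left to the analysis plan. That is fair for the fallback, but the export date and the look-back are fixed in this document.

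A reader might go further and infer that the timing does bias the comparison, and that it hides or reverses a real increase. The documents do not support this. The simplest bound is L × f / 26, where a fraction f of entries from the last L weeks is missing. It reaches 6 × 1 / 26 = 23%, turning a true +10% into −15%, only if nothing at all is recorded for six weeks.

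A reader might also turn such percentages into cases lost from the planned 1800. That is invalid: the 1800 are CHD patients per quarter, and a patient with any earlier entry in the same quarter is still counted. For the same reason the reach count in the primary outcome (section 2.2.1) is little exposed.

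**Conclusion.** The point holds as a conditional and minor one. The difference in record age follows from section 2.3 if the export falls at or near the close of the intervention window. Whether it matters depends on late entry, which the article neither reports nor excludes.

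Under the assumed delays, the after/before ratio is understated by about 1 to 2% (10% of entries late by a mean of 2 to 4 weeks) or about 5 to 9% (30% late by a mean of 4 to 8 weeks), and by nothing with prompt entry. The direction is against the intervention, provided that late changes mainly add entries rather than delete them. The primary feasibility objective is essentially untouched.

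**What to change.** In section 2.3, define both six-month windows from the training day, select entries by service date rather than by date of entry or by look-back from the export day, and run the single export after a stated run-out, for example 4 to 13 weeks. In the four partial-delay scenarios, 4 weeks reduces the shortfall to between 0.1% and 5.2%, and 13 weeks to at most 1.7%.

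If the timetable does not allow a run-out, add a sensitivity analysis that drops the same final weeks from both windows. If the sponsor can document that entries are made at the time of service, a sentence saying so would also settle the point.

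The cost is a delay of some weeks to one quarter in each office's export. The fallback costs somewhat less data in the sensitivity analysis: dropping 4 weeks gives up 4/26 = 15% of each window there, and the main analysis is unchanged.

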### 2.4. Data Management

Data management is carried out in accordance with the General Data Protection Regulation (GDPR). Given that our study design includes three different data sources per PCP office (questionnaire, qualitative interview and routine care data), we developed a detailed data protection concept that allows us to connect data from all three sources without identification of the underlying practice. Two independent data trust units within CoRe-Net will be responsible for storing the data, pseudonymising it twice and providing it to the researchers for analysis. A detailed description of the data protection concept is provided in Figure 3.

### 2.5. Data Analysis

Data analysis will be based on a combination of quantitative and qualitative analysis methods. The transcripts of the interviews in Parts I and II will be entered into MAXQDA software (VERBI GmbH, Berlin, Germany) and analysed following Miles and Huberman [42]. The software program MAXQDA will be used for the qualitative data analysis and supports the systematic evaluation and interpretation of the transcript. Qualitative content analysis will be chosen to explore the unique perspectives of the participants and to systematically extract the content to a descriptive level. To provide validity of data interpretation, transcripts will be independently coded by two researchers. A coding framework will be developed that combines deductive and inductive approaches. The deductive approach will draw on extant concepts for implementation of patient-centred care [43] as well as the Consolidated Framework for Implementation Research [44].

Descriptive and explorative methods will be used to analyse the quantitative routine data. To investigate the influence of the intervention on PCP behaviour, we will conduct repeated measures analyses to compare the frequency of diagnostic and therapeutic actions, referrals and medication prescription before and after the training course. In this context, the influence of organisational characteristics as well as the intervention adherence, as reported in the interviews, will be taken into consideration. In addition, we will record and analyse reasons for dropout or non-adherence to the study procedures. Data from PCP offices will be included in the analysis if a minimum of 80% (≥20 weeks) of the intervention phase has been completed before dropout. To reduce the risk of dropout, regular check-ins with the PCP offices will be carried out via e-mail or phone.

In case of missing data in the questionnaires on organisational characteristics, PCPs will be re-contacted to fill in the missing data. To reduce the risk of incomplete data in routine care datasets, as recommended in a study design phase [45], we have carefully restricted the export to meaningful variables relevant to our research question that are consistently collected in routine clinical practice. Additionally, we have made provisions to ensure that the extraction filters also identify the relevant data in case of spelling mistakes in the documentation. Prior to analysis, plausibility checks will be carried out on routine care data exports to rule out technical errors during the export process that may lead to incomplete data.

For the socio-economic impact assessment, primary and secondary data on the effects of the intervention will be collected and evaluated according to the principle of cost-benefit analysis [46]. A methodological framework is used in conjunction with evaluation software originally developed for business model development for IT-supported utility services [47].

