## 2. Materials and Methods

### 2.1. Study Setting

This study is part of the CoRe-Net research projects MenDis-CHD II, a study on quality of care in diagnosis and therapy of MCD in CHD, and OrgValue II, a study on characteristics of value-based care from the perspective of care institutions. It consists of two consecutive parts. Part I aims to develop a minimally invasive intervention to improve identification and management of MCD in CHD patients in the primary care setting. Additionally, potential determinants of implementation in PCP offices will be identified. In this context, “minimally invasive” refers to an intervention that hardly interferes with routine care practice and is designed to be time- and cost-efficient. The intervention will then be implemented and evaluated in PCP offices in Cologne, Germany and surrounding suburban municipalities in part II of the study. The total duration of Part II is twelve months, divided into a six-month pre-intervention observation period and a six-month intervention period. Our aims are to evaluate the feasibility of the intervention and, if given, assess whether the intervention changes PCPs’ management of CHD patients.

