#### 2.1.2. Part II: Intervention Implementation

**Participants.** For the implementation of the minimally invasive intervention designed in Part I, we intend to enrol *n* = 10 PCP offices (single or group practices). The sample size is based on calculations of the number of patients with CHD per practice per quarter. Based on previous reports, we assume that the number of patients per quarter per PCP will be 900 [38]. Data from the DETECT study on 55,518 patients in German primary care showed that 12.4% were diagnosed with CHD [39]. As a conservative measure, we decided on an estimate of 10% CHD patients, yielding *n* = 90 CHD patients per PCP per quarter. Multiplied by the number of PCP offices (*n* = 10), we expect 900 CHD patients per quarter, providing us with 1800 cases in the six-month pre-intervention observation period and 1800 cases in the six-month intervention period. To control for the influence of gender, we aim to balance recruitment of PCPs.

Inclusion criteria:Single or group PCP office in Cologne or the surrounding suburban municipalities

Exclusion criteria:Advanced training in basic psychosomatic careSpecialist additional qualification of psychotherapyParticipation in an interview in Part I

**Recruitment.** Recruitment strategies will focus on several channels, including presentation of the project at PCP events or symposia, recruitment via CoRe-Net, and invitation e-mails or letters to local PCP networks and PCP offices associated with the University Hospital Cologne.

**Intervention implementation.** PCPs will be invited to a training course as developed in Part I of the study. They will be encouraged to use the study material as described above during the six-month intervention period to aid them in identifying and managing CHD patients with potential MCD. However, we will not monitor usage and will instead emphasise that the intervention should be implemented in accordance with the PCPs’ routine work structure. By doing so, we aim to stay close to a “real-world setting” to analyse feasibility and increase generalisability of the results. After completing the intervention period, each PCP will be interviewed to assess their experiences and evaluate the feasibility of the intervention.

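### The office inclusion cut is given as 80% and as at least 20 weeks, but 20 weeks is about 77% of a six-month phase

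*Protocol article*

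**What the plan says.** The article gives one threshold for analysing an office that drops out, in two forms offered as equivalent: "a minimum of 80% (≥20 weeks) of the intervention phase has been completed before dropout" (Section 2.5, Data Analysis).

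The phase is defined only in months. Section 2.1 (Study Setting) describes Part II as twelve months, "divided into a six-month pre-intervention observation period and a six-month intervention period". Section 2.3 (Data Collection) fixes the starting point: "The day of the training course with the PCP marks the start of the six-month intervention phase". The length in weeks or days is not given.

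The analysis that uses these data will "compare the frequency of diagnostic and therapeutic actions, referrals and medication prescription before and after the training course" (Section 2.5). Section 2.3 describes the data source: "The data export will take place once per PCP office for each PCP separately at the end of the intervention phase", to "retroactively extract all relevant information from the preceding twelve months (six-month pre-intervention observation period and six-month intervention period"). The planned numbers in Section 2.1.2 assume two periods of equal length: "1800 cases in the six-month pre-intervention observation period and 1800 cases in the six-month intervention period".

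**The concern.** A percentage and a number of weeks that are printed as the same cut should select the same offices. Here they do so only if six months is counted as 25 weeks, or as 24 weeks with rounding up. On a calendar six months they differ, and an office leaving in the gap could be kept or removed depending on which form is applied. That choice would be open after the data have been seen. With 10 planned offices, one office is 10% of the sample.

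A related point follows from the same rule. It admits offices with about 20 weeks under the intervention alongside a pre-period of about 26 weeks. Unless the frequencies are scaled for time or for patients seen, or the windows are matched, the difference in length could look like a change in physician behaviour. It would run against the increase in screening and follow-up actions that the Discussion expects.

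**Working it through.** **Inputs**
- Cut: 80%, also given as at least 20 weeks (Section 2.5).
- Phase length: six months from the training day (Sections 2.1 and 2.3). By the calendar, six consecutive months are 181 to 184 days, or 25.9 to 26.3 weeks. I take 182 days (26 weeks) as the central value. This is an assumption, because the article gives no figure in weeks.
- Offices: 10 (Section 2.1.2).

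**Step 1. Does the plan's own planning point to about 26 weeks?** The case numbers are built from quarters: 900 patients × 10% × 10 offices × 2 quarters = 1800 cases per period. This reproduces the stated 1800. Each six-month period is therefore two quarters, or about 26 weeks.

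**Step 2. Can the equivalence be reproduced?** Compute 0.80 × length and 20 ÷ length.

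| Phase taken as | 80% of phase (weeks) | 20 weeks as share |
|---|---|---|
| 24 weeks | 19.2 | 83.3% |
| 25 weeks | 20.0 | 80.0% |
| 181 days (25.86 weeks) | 20.69 | 77.3% |
| 26 weeks | 20.8 | 76.9% |
| 184 days (26.29 weeks) | 21.03 | 76.1% |

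The two forms coincide exactly only at 25 weeks. At 24 weeks they agree only if 19.2 is rounded up to 20. Neither length appears in the article. For a calendar six months they do not agree.

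**Step 3. Size of the gap.** 20.8 − 20 = 0.8 week, and 0.8 × 7 = 5.6 days. Only an office leaving inside that interval is classified differently. If dropout times were uniform over the phase (an assumption), that would be 0.8/26 = 3% of dropouts.

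**Step 4. Effect of unequal windows.** This step is conditional on three things: unscaled counts are compared, no data after dropout are used, and the office leaves at week 20 with an unchanged rate.
- Post count ÷ pre count for that office: 20/26 = 0.769, an apparent fall of about 23%.
- True rise needed for that office to look unchanged: 26/20 − 1 = 30%.
- Pooled over 10 equal offices with one such office: (9 × 26 + 20)/260 = 254/260 = 0.977, or 2.3% lower.

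Correcting the cut does not remove this effect. At exactly 80% the ratio would be 20.8/26 = 0.80. If frequencies are expressed per unit time, the effect of unequal length disappears.

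**The case against.** The mismatch is about six days and looks like loose rounding. Few dropouts, if any, would fall in the gap, and the article plans regular check-ins to limit dropout. The primary objective is feasibility. The before-after comparison is secondary, descriptive and explorative, has no control group, and carries no test or power claim. All of this stands, and it limits the consequence. It does not make the two printed figures agree, and leaving detail to a fuller document does not remove a contradiction inside one sentence.

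A reader might infer that the plan compares raw counts from a short post window with a full pre window. The article does not say so. It speaks only of frequency, its planning counts are per quarter, and its routine data are at patient level, so a rate or a proportion fits the wording equally well. How the measure is scaled may properly be left to the full protocol or analysis plan.

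A reader might also infer that an office that drops out is exported at dropout, with twelve months counted back from that date, which would lengthen its pre window. No passage describes this. Section 2.3 ties the export to the end of the intervention phase, specifies six months on each side, and makes the training day the dividing point. Because the export is retrospective, records for the remaining weeks might still be available after an office stops. The article does not settle whether they would be used.

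**Conclusion.** The inclusion rule contains a wrong figure. On a calendar six-month phase, 80% is 20.7 to 21.0 weeks and 20 weeks is 76% to 77%. The two forms give different answers for an office leaving between week 20 and about week 20.8. This rests only on reading six months as about 26 weeks, which the two-quarter case calculation supports.

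The unequal-window point is a risk to guard against. It is not an error in the text. The figures of 0.77 for one office and 2.3% pooled hold only under the conditions in step 4 of the working, and the article gives no dropout rate from which to say how many offices might be affected. It would overstate the case to say that the planned comparison is biased.

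The impact is small, because no confirmatory conclusion depends on the comparison. It is still worth correcting, because the rule determines which of 10 offices are analysed and the correction is very cheap.

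**What to change.** 1. State the phase length in days and give a single cut. One option is at least 80% of a 182-day phase: 0.80 × 182 = 145.6, so at least 146 of 182 days. The other is to keep at least 20 weeks (140 days) and describe it as about 77%. A threshold of 21 weeks should not be labelled 80%, since 21/26 = 80.8%.
2. State that frequencies are analysed per unit time or per CHD patient-quarter, for example with a log-time offset in a count model. Alternatively, compare windows of equal length on either side of the training day.

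The cost is one reworded sentence for the cut, and one sentence or an offset term for the analysis. No additional data collection is needed.
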